#### Waiting-list (delayed start) control group

The control condition of this study is a waiting list. During the waiting period, the participants will receive TAU and will also be asked keep an IBS diary for self-monitoring [27]. The participants in the control condition will receive GCBT after week 13.

#### Treatment as usual (TAU)

TAU is defined as the continuation of current medications prescribed by a general practitioner or gastroenterologist. All participants will continue TAU during the study period. We will collect and record information about any changes in IBS treatments/management during the study.

#### Other treatments

We will ask all participants not to change their TAU as much as possible during the study period. We will record any change in medications for IBS. Other psychotherapies for IBS are prohibited during the study period. There is no restriction on the treatments for comorbidities.

#### Criteria for discontinuing the allocated interventions

The allocated intervention will be discontinued if any of the following criteria are met:
If the participant wishes to withdraw from the intervention for any reasonIf the participant cannot continue the intervention for any reason (e.g., death, exacerbation of comorbidities, adverse events, etc.)If the study itself is discontinued.If the steering committee determines that it is appropriate to stop the intervention.

We will record the reason and date of discontinuation. We will follow up and assess the participants after the discontinuation of the allocated interventions as long as they do not withdraw their consent to be evaluated.

### Outcomes

As there is no standard outcome measure for IBS [28], we will use two clinically important measures as the co-primary outcomes of this study, namely, the severity of symptoms of IBS and disease-specific QOL due to IBS [29]. When one variable cannot fully capture the range of therapeutic efficacy, it is sometimes necessary to use several variables [30, 31]. We will consider the intervention efficacious if at least one of the co-primary outcomes shows statistically significant superiority at the pre-designated alpha-level controlling for multiple outcomes [30].

### Primary outcomes

The two co-primary outcomes are changes in IBS-SSS and/or IBS-QOL scores from baseline to week 13.

#### The irritable bowel syndrome severity scoring system (IBS-SSS)

The IBS-SSS is a 5-item self-administered questionnaire. The IBS-SSS relates to individual domains for the severity of abdominal pain, the duration of abdominal pain, bloating, satisfaction with bowel habits, and QOL. The IBS-SSS total score ranges from 0 to 500: < 75 normal, 75–174 mild IBS, 175–299 moderate IBS, 300–500 severe IBS. According to the scale developers, a 50-point or greater change on this scale is considered clinically significant [32, 33].

#### The irritable bowel syndrome quality of life (IBS-QOL)

The IBS-QOL is a 34-item, 8-subscale self-administered questionnaire. The IBS-QOL relates to individual domains for dysphoria, interference with activity, body image, health worry, food avoidance, social reaction, sexual relationships. The total score ranges from 0 to 100, with lower scores reflecting poorer QOL [34, 35]. Evidence shows that a range from minimal to optimal response may be in the 10–14 point range [36].

### Secondary outcomes

Our secondary outcomes include (a) the Gastrointestinal Symptom Rating Scale (GSRS: a clinical rating scale for gastrointestinal symptoms with 15 items, 7 subscales) [37, 38]; (b) the Irritable Bowel Syndrome-Global Improvement Scale (IBS-GIS: measures patient-perceived severity of symptoms with a 7-point Likert-type scale ranging from 0 [no discomfort] to 6 [very severe discomfort]) [39]; (c) the Patient Health Questionnaire-9 (PHQ-9: 9 items, 4 subscales, scale 0–27; lower scores indicate lower symptom severity of depression) [40]; (d) the Generalized Anxiety Disorder-7 (GAD-7: 7 items, 4 subscales, scale 0–21; lower scores indicate lower generalized anxiety) [41]; (e) EuroQol-5 Dimension-5Level (EQ-5D-5 L: health status is assessed with 5 items, 5 subscales) [42] and a visual analogue scale (VAS); (f) the Composite Primary Reduction Score (CPRS: 4 items, 5 subscales, lower scores indicate lower abdominal symptoms).

We will also collect data on medication use and health services used. Along with baseline data, all outcome data will be sought by the Internet or a postal questionnaire at 4, 9, 13, 27 weeks, and where these methods fail, data for the main outcome measure will be sought by telephone. We will also seek information associated with the homework completion rate and adverse events (AEs).

### Participant timeline

Figure 1 shows the participant timeline, and Table. 1 shows the enrolment, intervention, and assessment schedule.

**Fig. 1 Fig1:**
[figure not shown]
The participant timeline

**Table 1 Tab1:**
[figure not shown]
The enrolment, intervention, and assessment schedule

Note: Evaluation is performed by the person indicated by each colored cells

*Abbreviations*: *C* Coordinator, *C*
 Coordinator calls patient, *E* Evaluator, *Pt* Patient, *Th* Therapist

### Sample size

The sample size is based on the two co-primary outcomes of IBS-SSS and IBS-QOL. To adjust for multiplicity conservatively, we used the Bonferroni method and set the significance level at 2.5% (α level: 0.025). The correlation coefficient between the absolute scores of IBS-SS and IBS-QOL has been reported to be 0.36 [35]. With power set at 80% and α set at 0.025, for two co-primary outcomes correlating at 0.40, a sample size of 55 subjects per group is required to obtain sufficient power to detect a moderate effect size of 0.5 [43] between the groups. Because each randomization will take place for a group of 8 (4 being assigned to the intervention and 4 to the control), a minimum of 14 groups is required to reach this number, and the total sample size is therefore 8 × 14 = 112. With the mixed-effect models for repeated measures, we can obtain the same power with 30–50% fewer participants than with the ordinary t-test or analysis of covariance [44]. In this trial, less than 30% dropout is expected. We therefore set the final target sample size, including drop-outs, as 112 patients in total, or 56 patients in each group. The power calculations were conducted with SAS PROC POWER by an independent statistician (TS). The appendix shows the SAS program.

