### Statistical methods

All analyses will be performed according to the intention-to-treat principle; all participants will be included in their randomized groups whether or not they have received their allocated treatment.

The mean difference in change scores on the IBS-SSS and the IBS-QOL will be estimated by the mixed-effects model for repeated measures (MMRM) [45]. In this model, the scale scores at weeks 4, 9 and 13 are the dependent variables. The allocation group (intervention = 0 vs control = 1), measurement point (middle = 1, post = 2, follow = 3) and the interaction term of both factors are fixed effects. The measurement point is treated as a categorical variable. The baseline measurement is used as the covariate. A participant is taken as the random effect. The covariance matrix describes the correlation between observations at different measurement points [45]. The Hochberg method will be applied for adjustment of multiplicity, and the threshold for statistical significance will be set at *p* < 0.05 (two-sided).

Secondary outcomes, including GSRS, IBS-GIS, PHQ-9, GAD-7, EQ-5D-5 L and CPRS, are important to measure the wider IBS effects and will be similarly analysed (as appropriate for continuous or dichotomous outcomes). These analyses will be exploratory in nature to complement the primary analyses; therefore, we will not adjust for multiple testing.

In this trial, participants who attend at least 1–5 sessions will be defined as a ‘Completer’, and we will conduct an analysis of covariance (ANCOVA) using the completers’ data and check the robustness of the result by MMRM.

The follow-up assessments at week 27 will be descriptively compared with the assessments at week 13, as the randomized comparison between the two arms no longer holds after the control participants have received the GCBT.

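### The target of 112 covers dropout only through a claimed 30–50% MMRM saving that does not exist against ANCOVA at week 13, so 80% power with dropouts included is not secured

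*Protocol article*

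**What the plan says.** All of the sample-size reasoning is in the protocol article, section Sample size.

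- The inputs are two co-primary outcomes correlating at 0.40 and an effect size of 0.5: "With power set at 80% and α set at 0.025". This gives 55 per group. No dropout term enters.
- The number becomes 56 per group because patients are randomized in groups of eight: 14 × 8 = 112.
- Next comes the efficiency claim, that with mixed models for repeated measures "we can obtain the same power with 30–50% fewer participants than with the ordinary t-test or analysis of covariance".
- Then: "In this trial, less than 30% dropout is expected".
- The conclusion: "We therefore set the final target sample size, including drop-outs, as 112 patients in total, or 56 patients in each group".

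The success rule is in the Outcomes section: "We will consider the intervention efficacious if at least one of the co-primary outcomes shows statistically significant superiority". Primary outcomes fixes the contrast as change from baseline to week 13. Statistical methods models the scores at weeks 4, 9 and 13 with group, visit and their interaction, and adds: "The baseline measurement is used as the covariate".

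**The concern.** The plan needs 55 evaluable patients per arm and enrols 56, so the margin in numbers is one patient per arm. The rest of the cover for dropout is the claimed MMRM saving, and the section gives no correlation or calculation behind it.

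The claim names two comparators. One is ANCOVA. But the planned model already adjusts for baseline and is read at a single visit, which is nearly what an ANCOVA at week 13 estimates. Repeated measures can then help only by recovering information from patients who have earlier visits but no week-13 score.

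At stake is a headline design property: 80% power for a 0.5 SD effect with dropouts already counted. If it rests on a gain that the planned estimator lacks, readers of the protocol are given more assurance than the design supports.

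**Working it through.** **Inputs.** From Sample size: d = 0.5 on each outcome, correlation 0.40 between outcomes, alpha 0.025 per outcome, 56 enrolled per arm, dropout under 30%. From Outcomes: success on at least one outcome. Two-sided testing is stated in Statistical methods and is assumed for planning too. Correlations between visits are not given; 0.3–0.8 is assumed (compound symmetry and AR(1)).

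**Step 1: reproduce the 55.** Each test statistic has mean 0.5 × √(n/2) and critical value 2.241. Power is 1 − P(neither significant), from a bivariate normal with correlation 0.40. At n = 55 the mean is 2.622 and power is 82%; 80% is first reached at n = 53. Simulated t-tests give 54 for 80% and about 81% at 55. The stated 55 is confirmed, and t-test power matches it.

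**Step 2: remove dropout, with no efficiency credit.**

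| Missing at week 13 | Evaluable per arm | Power, at least one |
|---|---|---|
| 0% | 56 | 82–83% |
| 10% | 56 × 0.9 = 50.4 | 78% |
| 20% | 56 × 0.8 = 44.8 | 73% |
| 30% | 56 × 0.7 = 39.2 | 67% |

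The planned Hochberg procedure, in place of Bonferroni, adds only about one point (82.9% against 81.6% at 56 per arm, by simulation).

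**Step 3: MMRM against ANCOVA at week 13.** With complete data the two give the same week-13 variance, so the saving is 0%. With a fraction m missing at week 13, MMRM does best when every loss occurs after week 9. In large samples its saving over completer ANCOVA is then m × R², where R² is the squared multiple correlation of week 13 with weeks 4 and 9, given baseline.

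- AR(1) at 0.8: R² = 1 − 0.36/0.738 = 0.512, so the saving is 0.3 × 0.512 = 15.4%.
- Baseline correlation 0.3, follow-up visits correlating at 0.8: the partial correlation is (0.8 − 0.09)/(1 − 0.09) = 0.780, R² = 2 × 0.780²/1.780 = 0.684, and the saving is 0.3 × 0.684 = 20.5%.
- Gradual loss (90%, 80%, 70% observed), compound symmetry or AR(1) at 0.3–0.8: 1.2–8.3%.
- All losses before week 4: 0%.

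The range is about 2–20%. Since R² cannot exceed 1, 30% is an unattainable ceiling at 30% missing; 30–50% over ANCOVA cannot be had.

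**Step 4: against an unadjusted t-test.** Baseline adjustment cuts the variance by r², with r the baseline to week-13 correlation. A 30–50% saving from this alone needs r = √0.30 = 0.55 to √0.50 = 0.71.

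**Step 5: power with credit given.**

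*If d = 0.5 is in baseline-adjusted SD units*, effective n is 39.2/(1 − saving). Savings of 1.6% and 20.5% give 39.8 and 49.3 per arm, so power at 30% missing is about 68–77%.

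*If d = 0.5 is in raw SD units*, the baseline gain also counts. Without partial-data credit, 80% needs 56(1 − m)/(1 − r²) ≥ 53:

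- 10% missing: r² ≥ 1 − 50.4/53 = 0.049, r about 0.22
- 20% missing: r² ≥ 1 − 44.8/53 = 0.155, r about 0.39
- 30% missing: r² ≥ 1 − 39.2/53 = 0.260, r about 0.51

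With MMRM credit under gradual loss, r = 0.3–0.4 gives about 82–87%, 78–85% and 72–81% at 10%, 20% and 30% missing. At 30%, r of about 0.4 suffices when follow-up visits correlate strongly. A value of 0.3 is enough only at the favourable extreme: follow-up correlation 0.8 with all losses after week 9, where 39.2/(0.91 × 0.795) = 54.2 per arm.

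**The case against.** The defence has four good arguments.

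**The benchmark is a t-test.** The disputed sentence names the t-test first, and t-test power reproduces the 55. Against that benchmark a baseline-adjusted model can offset dropout. This stands: it is wrong to say that the plan makes no allowance. It states one, half of it against the wrong comparator and all of it without the correlation that it needs.

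**30% is a bound.** The section expects less than 30%, so 67% is the limiting case with no credit of any kind. At 10–20% missing, a baseline correlation of 0.3–0.4 is about enough on the raw scale. This stands too.

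**Dropout may not mean missing data.** The sections on discontinuation criteria and on retention keep collecting outcomes after patients stop the intervention, with reminders, payments and telephone collection. Missing week-13 scores may be fewer than dropouts. Against this, patients who leave treatment but remain in the intention-to-treat analysis can dilute the effect, and Sample size does not say which meaning it uses.

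**No arithmetic slip.** Both 55 and 8 × 14 = 112 check. The fault is an efficiency assumption that does not fit the planned estimator.

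Two stronger readings are tempting. A reader might infer that power is below 80%, so that the trial must enrol 55/0.7 = 79 per arm, or 160 in cohorts of eight. The document does not support this, because an unstated but possible baseline correlation could close the gap. A reader might also infer a further loss from clustering within therapy groups. The document gives no intracluster correlation, so no size can be put on that and it is no part of this point.

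**Conclusion.** The point holds as wrong as written. For a week-13 contrast with baseline as covariate, the claimed 30–50% saving over ANCOVA is 0% with complete data and about 2–20% at 30% monotone loss. The 80% power with dropouts included is not secured by anything that the plan states, but neither is it shown to be missed. The outcome turns on three things left unstated: whether d = 0.5 is raw or baseline-adjusted, the baseline to week-13 correlation, and how many week-13 scores will be missing. On the adjusted scale, 30% missing leaves about 68–77%. On the raw scale, 80% at 30% missing generally needs a baseline correlation of about 0.4–0.5 or more.

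These figures rest on assumed between-visit correlations of 0.3–0.8, equal loss in both arms, monotone missingness and large-sample variances. Type I error, randomization and the analysis model are unaffected.

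**What to change.** In Sample size:

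1. Delete the claimed saving over ANCOVA.
2. Keep N = 112.
3. State whether d = 0.5 is in raw or baseline-adjusted SD units.
4. State the assumed baseline to week-13 correlation. If a gain over the t-test is to be kept, tie it to that value.
5. Say whether dropout means stopping the intervention or missing the week-13 outcome, consistently with the sections that continue assessment after discontinuation.
6. Restate the power of the week-13 MMRM contrast, for at least one co-primary, at 10%, 20% and 30% missing, with the assumed between-visit correlations.

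The cost is one reworded paragraph and a short power table. No extra patients are needed and the analysis does not change. The stated power may become less favourable: about 68–77% at 30% missing if d is on the adjusted scale.

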### Recruitment

Participants will be recruited from primary and secondary care in Kyoto and surrounding prefectures and through the Internet. We are planning to recruit the participants within 2 years. Should there be any difficulty recruiting the planned sample size, we will cooperate with hospitals and clinics outside of Kyoto city.

### Assignment of interventions

#### Allocation

##### Sequence generation

The independent statistician (TS) will generate the random allocation sequence using SAS 9.4. We will use permuted block randomization with a block size of 4 for stratified randomization by baseline severity.

##### Randomization and allocation concealment

Up to eight participants will attend the initial IBS psychoeducation session. A researcher who is not involved in participant recruitment, assessment or treatment will receive the allocation sequence in a sealed envelope from the principal investigator and will receive the data about the participants’ IBS-SSS scores from the gastroenterologist conducting the baseline assessment. The group will be split by the median score into the more severe and the less severe halves, and the independent researcher will then allocate each participant to either GCBT or WL according to the corresponding sequence and will notify the treatment team of the allocation results.

##### Blinding

Blinding is notoriously difficult in research on psychotherapy. In this research, neither participants nor researchers will be blinded to the intervention that each participant is receiving. Furthermore, the primary and secondary outcome assessments are not blinded because these are self-administered PROM measures.

The data management team will prepare the datasets in which all components are denoted only by a letter. The statistician will be blinded to the allocation during the statistical analyses until the statistical analysis report is finalized.

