### Limitation

There are some limitations to this study. First, this study is an open-label randomized controlled trial, in which participants, personnel and outcome assessor are unblind and only the data analyst is blinded. Unblinding of participants and personnel can result in performance bias, and results may be biased in favour of the intervention group [52]. Moreover, there is no standard indicator (eg, biomarker etc.) that can be used as an objective primary endpoint in IBS. Thus, the primary outcome of this study is IBS disease severity and disease-related quality of life, which are measured by patient reported outcomes (PROs). Although the importance of PROs has been recognized, the absence of blinding of outcome assessment can result in detection bias [53]. To minimize this bias, we will use only scales that have been established with confidence and validity.

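### The claimed analyst blinding cannot last until the report is finalised, because the planned completer analysis needs attendance data that identify the lettered arms

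*Protocol article*

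**What the plan says.** The Blinding section of the Protocol article accepts that participants and researchers know the allocation and that the outcomes are self-administered. It then makes one masking claim. The data management team supplies files in which components appear only as letters, and "The statistician will be blinded to the allocation during the statistical analyses until the statistical analysis report is finalized". The Limitation section repeats the claim: "only the data analyst is blinded".

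The Statistical methods section describes the primary MMRM of IBS-SSS and IBS-QOL at weeks 4, 9 and 13, with the group factor coded "intervention = 0 vs control = 1". It then adds an ANCOVA in completers to check robustness, where "participants who attend at least 1–5 sessions will be defined" as completers. The section on the waiting-list control group places the controls' GCBT after week 13. The Secondary outcomes section adds that homework completion will be collected.

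On roles, the Sequence generation section says that the independent statistician "will generate the random allocation sequence using SAS 9.4". The Sample size section credits the power calculation to an independent statistician with the same initials. The list is applied by someone else: "the independent researcher will then allocate each participant to either GCBT or WL according to the corresponding sequence".

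**The concern.** Analyst blinding is the only masking offered to the reader. It is promised for the whole period up to the final report, yet one of the analyses in that report depends on data that only one arm can have. If the promise fails, readers credit the trial with a safeguard that it did not keep. Any analysis decision still open at that stage would be made by someone who knows which result favours GCBT. The completer threshold, printed as a range of one to five sessions, is one such decision.

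A second, weaker worry concerns roles. The article speaks of the statistician in the singular, and the only statistician it identifies is the one who creates the allocation list. It does not say whether that person also analyses the data.

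**Working it through.** The plan attaches no figure to this point, so the check sets the sections side by side.

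**1. Period covered.** The claim runs through the statistical analyses until the report is final. It therefore covers every analysis in the report, not only the primary one.

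**2. Data that each analysis needs.**

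| Planned analysis | Fields needed | Do these fields show which letter is GCBT? |
|---|---|---|
| Primary MMRM, both co-primary outcomes | letter, visit, baseline score, scores at weeks 4, 9 and 13 | No |
| Secondary outcomes, analysed similarly | the same kinds of field | No |
| Descriptive week 27 comparison | scores at weeks 13 and 27 | Not from the fields alone |
| Completer ANCOVA | the above plus session attendance | Yes |

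**3. Why attendance reveals the key.** There are only two letters, so placing one participant with certainty decodes all 112. Up to week 13, GCBT sessions attended by controls = 0 by design. The information could reach the analyst in several forms:
- *Session counts or homework records:* the letter with any entry above zero is GCBT.
- *A completer flag with controls set to no:* the letter with any completer is GCBT.
- *A completer flag with controls set to yes:* the letter with a mix of yes and no is GCBT. This fails to reveal the key only if every GCBT participant is a completer, in which case the completer analysis drops nobody.
- *A file already cut down to completers:* compared with the full file, the letter that loses participants for reasons other than missing outcomes is GCBT.

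Lettering does not protect this analysis in any of these forms.

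**4. What the sequence generator could infer.** The Sequence generation section states: "We will use permuted block randomization with a block size of 4 for stratified randomization by baseline severity". The section on randomization and allocation concealment adds: "The group will be split by the median score into the more severe and the less severe halves". With a full intake of eight, each half holds four people, which is one block. A block has 4!/(2! × 2!) = 6 arrangements, and 112/4 = 28 blocks give 6^28, about 6.1 × 10^21, possible lists. The person who made the list knows which one was used. To match it to participants, that person also needs intake group, severity half and order within the half. Given intake group, the severity half follows from baseline IBS-SSS, which the model uses. With intake group and order added, the match is unambiguous. Without them, the list alone does not show who received what. The article neither includes these fields in the analyst's file nor withholds them.

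**5. The 0/1 code.** Replacing x by 1 − x reverses the sign of the between-group contrast at week 13. Its absolute size, standard error and two-sided p-value do not change. The code can be applied to letters A and B and labelled later, so it is not evidence of unblinding.

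**The case against.** The best reply is that the article does not list the variables in the masked file. Staged release may be set out in a full protocol or analysis plan that is not shown. The completer ANCOVA is only a robustness check, and the confirmatory MMRM can be run without attendance or homework. The Limitation section presents analyst blinding within an admission of bias, and the mitigation it names is the use of established scales. The main bias, unblinded self-report, is disclosed and would be untouched by any change here.

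Most of this stands and limits the importance of the point. It does not rescue the claim as written. Staged release would protect the primary result, but blinding would still end before the report is final, which is later than the primary MMRM.

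A reader might also infer more than the documents support:
- *That the sequence generator is the analyst, so that blinding is lost from the start.* The singular wording suggests it, but no section says so. A separate researcher applies the list, and the data arrive letter-coded.
- *That the statistician's full access to the final dataset, in the Access to data section, breaks the blinding.* That section gives no timing.
- *That the trial's false-positive rate is inflated by a stated amount.* Choosing the most significant of several analyses in either direction is open to an analyst who sees only letters, so such a figure does not measure loss of blinding. Completer thresholds also do not enter the success rule, which rests on the two co-primary outcomes with multiplicity control.

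**Conclusion.** The analyst blinding is insecure as described and cannot hold until the report is finalised. This follows from the article's own sections and does not depend on who the analyst is. It assumes that completer status is judged on sessions up to the week 13 endpoint and that the completer ANCOVA is part of the report.

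The consequence is contained. It touches the completer analysis directly. It touches the primary MMRM only if attendance, homework or list-matching fields reach the analyst before that model is final. No numerical size is claimed. The missing separation between sequence generator and analyst is an ambiguity to resolve, not a demonstrated breach. The point is still worth correcting, because it concerns the only blinding the trial claims and the remedy costs almost nothing.

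**What to change.** 1. Give the analyst a letter-coded file without attendance, homework, intake-group or enrolment-order fields.
2. Finalise the primary MMRM results for IBS-SSS and IBS-QOL on that file, and only then release attendance for the completer analysis.
3. State that the person who generates the sequence will not run the primary analysis. If the same person must do both, withhold the fields that would let the list be matched to participants. Sequence generation need not move to the data management team, whose independence from recruitment is not stated.
4. If separation and withholding are not adopted, limit the wording in the Blinding and Limitation sections to blinding through the primary MMRM, and claim that only if the key-revealing fields are in fact held back until then. Even with staged release, the end point of the claim should be the primary MMRM results, because the completer analysis cannot be masked.

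The cost is a staged data export, a few sentences of text, possibly one reassigned task, and a short delay to the completer analysis. Sample size, outcomes and the primary model do not change.
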